### **4.11 Subgroup analyses**

No subgroup analyses are planned.

### **4.12 Effect-sizes**

For median comparisons, the magnitude of the treatment effects will be presented as between-group differences in median relative the interquartile range. For mean comparisons, the magnitude

## **Appendix**

of the treatment effects will be presented as standardised between-group effect sizes (Cohen's *d*) [11]. The latter method will be used to enable comparisons with previous trials in the field.

### **4.14 Reliability**

Inter-rater reliability of the YGTSS-TTSS will be estimated by intra-class correlation coefficients (ICC). ICC will be calculated on case examples before the study start, as well as on actual study participants during the trial.

### **5.2 Analyses**

The short-term health economic evaluation (objective #3) will compare BIP TIC and the comparator at the primary endpoint (3FU). These results will be published together with the efficacy results (objective #1) in paper 1. As a long-term evaluation, we will then perform the same analyses at the end of the follow-up period (12FU) using cumulative information collected throughout the follow-up. These results will be published together with the results of the naturalistic follow-up (objective #2) in paper 2.

The health economic evaluation will be performed from three different perspectives, with gradually increasing costs included for each perspective:

1. The first perspective is the health organisation payer perspective, which includes direct treatment costs, of BIP TIC and the comparator, for the clinic. This comprises personnel costs such as therapist time, administration time, IT platform maintenance, and other overheads.
2. The second perspective will additionally include other healthcare resource use outside the clinic for the children, such as costs for medical appointments (outside the trial) and medications.
3. The third perspective will further comprise other societal costs, including productivity losses for the children related to absenteeism and presenteeism from school and leisure activities, and productivity losses for the parents due to absenteeism from work.

## Appendix

The Trimbos/iMTA Questionnaire for Costs associated with Psychiatric Illness (TiC-P [12]) will be administered (in an adapted version for young people and parents) at each assessment point (except 3 and 5 weeks into the treatment) to collect information on frequencies of resource use for the children and absenteeism from work for the parents. Resource use costs will be estimated by multiplying frequencies by national Swedish tariffs and market prices. Total costs for each group will be aggregated over the trial period.

For each of the three perspectives above, we will conduct two types of analyses:

1. A cost-effectiveness analysis, using responder rate as the outcome [13].
2. A cost-utility analysis using Quality Adjusted Life Years (QALYs) as the outcome [13].

Health gains in terms of QALYs will be estimated by mapping KIDSCREEN-10 scores [14] onto Child Health Utility 9 Dimensions (CHU9D) utility weights [15]. Total QALY gains over the trial period will be estimated by using the area under the curve method [16]. Differences in QALYs and costs between both trial arms will be investigated using generalised linear models with suitable distributions [17].

To ascertain whether BIP TIC is cost-effective, relative to the comparator, incremental cost-effectiveness ratios expressed as cost per additional responder and cost per additional QALY will be presented. The uncertainty around the cost and effect estimates will be presented using a cost-effectiveness acceptability curve [13].

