#### ***KIDSCREEN-10 – child version***

The KIDSCREEN-10 [51] is a generic paediatric quality of life measure. KIDSCREEN-10 consists of 11 items (of which 10 of the items make up an index), each with a 5-level response category. The questionnaire has shown proper psychometric properties [52]. Quality adjusted lifetime years (QALYs) will be estimated by mapping KIDSCREEN-10 scores onto Child Health Utility 9 Dimensions (CHU9D) utility weights [53]. The questionnaire takes less than 5 minutes to complete.

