| Blindness checks                                        |                                     |          |               | X              | X                                    | X                 | X                         |
| Did the participant meet the therapist?                 |                                     |          |               | X              |                                      |                   |                           |
| BIP platform usage data + therapist telephone time      |                                     |          |               | X              |                                      |                   | X (Number of logins only) |
| Assessment format (face-to-face or video conference)    |                                     | X        |               | X              | X                                    | X                 | X                         |
| Child-reported outcomes                          |                                     |          |               |                |                                      |                   |                           |

|                                                               |  |   |               |   |   |   |   |
|---------------------------------------------------------------|--|---|---------------|---|---|---|---|
| C&A GTS-QOL 6-12 or 13-18, depending on the participant's age |  | X |               | X | X | X | X |
| SMFQ Child + additional suicide item                          |  | X | After 5 weeks | X | X | X | X |
| OCI-CV                                                        |  | X |               | X | X | X | X |
| Treatment credibility                                         |  |   | After 3 weeks |   |   |   |   |
| WAI-C                                                         |  |   | After 3 weeks |   |   |   |   |
| Treatment satisfaction                                        |  |   |               |   | X |   |   |
| Need for further treatment                                    |  |   |               |   | X |   |   |
| KIDSCREEN-10 child                                            |  | X |               | X | X | X | X |
| Caregiver/parent-reported                              |  |   |               |   |   |   |   |
| PTQ                                                           |  | X | After 5 weeks | X | X | X | X |

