### **6.6.3 3, 6 AND 12-MONTH FOLLOW-UPS**

Follow-ups will be administered 3, 6 and 12 months after the end of the 10-week treatment. As with the post-treatment assessment, these assessments are conducted face-to-face at the clinic or via videoconference software (depending on the participant's preference). The YGTSS interview will be video recorded. If technical problems with the videoconference software Zoom, the assessment will be made over telephone instead (with the family on speaker telephone). Child- and parent-reported questionnaires are answered online directly to our trial database BASS, preferably prior to the face-to-face/videoconference assessment. See **Table 1** for information regarding which measures are administered at each time point. For these follow-ups, there is a -1 month/+2 month time period for data collection.

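### The SAP names no baseline covariate for comparing QALYs and costs between arms, although baseline utility and baseline resource use are both collected

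*Combined protocol and SAP*

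**What the plan says.** The utility source is given in protocol 5.5.4: "Quality adjusted lifetime years (QALYs) will be estimated by mapping KIDSCREEN-10 scores onto Child Health Utility 9 Dimensions (CHU9D) utility weights". SAP 5.2 then builds the outcome: "Total QALY gains over the trial period will be estimated by using the area under the curve method". The comparison of arms is one sentence, the same in SAP 5.2 and protocol 8.3: "Differences in QALYs and costs between both trial arms will be investigated using generalised linear models with suitable distributions". The choice of distribution is mentioned; the terms in the model are not. The results feed the decision measures: "incremental cost-effectiveness ratios expressed as cost per additional responder and cost per additional QALY will be presented", for three cost perspectives and two horizons, together with an acceptability curve.

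Both baselines exist. Table 1 in protocol 6.3 marks "KIDSCREEN-10 child", and the parent version, at baseline, post-treatment and 3, 6 and 12 months. TiC-P is given "at each assessment point (except 3 and 5 weeks into the treatment", so baseline is included, and Table 1 confirms it. Protocol 6.1.2 requires the baseline measures to be answered before randomisation. Perspective 1 is different: it "includes direct treatment costs, of BIP TIC and the comparator, for the clinic", which has no baseline counterpart.

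**The concern.** A total QALY computed as an area under the curve starts from the child's baseline utility, and children who start higher tend to stay higher. If the arms differ at baseline by chance, an unadjusted comparison of total QALYs counts part of that gap as treatment effect. Protocol 6.2 describes randomly varying blocks but no stratification on utility or cost, so nothing in the design limits the gap beyond randomisation itself. Subtracting baseline is not a cure, because it over-corrects when the correlation between visits is below 1. The phrase QALY gains in SAP 5.2 does not say which of the two quantities is meant.

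Over a horizon of about five months any plausible QALY difference is small, and it is the denominator of the cost-per-QALY ratio. Leaving the model terms open also means that adjusted and unadjusted analyses could give different ICERs with no stated rule for choosing. SAP 4.2 promises code prepared before unblinding for objective #1 only, and SAP 1.1 labels later adaptations post-hoc.

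**Working it through.** The documents give no SD, correlation or expected difference for QALYs or costs, so there is no stated figure to reproduce. The 97% power in protocol 5.3 concerns the tic score.

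**Inputs from the documents.** Ten weeks of treatment, then "Follow-ups will be administered 3, 6 and 12 months after the end of the 10-week treatment". Taking 3, 6 and 12 months as 13, 26 and 52 weeks, the utility visits fall at weeks 0, 10 and 23 (3FU) and at 0, 10, 23, 36 and 62 (12FU). The planned sample is 220 randomised 1:1, or 110 per arm.

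**Assumptions.** Utility SD 0.08 to 0.16, equal at all visits. One common between-visit correlation ρ of 0.3 to 0.7. For illustration, a true utility difference of 0.03 at every visit from post-treatment on.

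**1. Baseline weight (trapezoid rule).** Baseline carries half of the first interval, 10/2 = 5 weeks.
- 3FU: w₀ = 5/23 = 21.7%, horizon 23/52 = 0.442 years.
- 12FU: w₀ = 5/62 = 8.1%, horizon 62/52 = 1.192 years.

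**2. Share of a baseline gap carried into the arm difference**, relative to a gap that persists in full. For total area it is w₀ + ρ(1 − w₀). For change from baseline it is that value minus 1.

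| ρ | 3FU, total area | 3FU, change from baseline | 12FU, total area |
|---|---|---|---|
| 0.3 | 45% | −55% | 36% |
| 0.5 | 61% | −39% | 54% |
| 0.7 | 77% | −24% | 72% |

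If treatment is paused for the permitted two weeks, w₀ at 3FU is 6/25 = 24%, and 47 to 77% is carried.

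**3. Shift from a one-standard-error imbalance at 3FU.** The SE of the baseline difference is SD × √(2/110) = 0.135 SD.
- SD 0.08, ρ 0.3: 0.0108 × 0.452 × 0.442 = 0.0022 QALY.
- SD 0.16, ρ 0.7: 0.0216 × 0.765 × 0.442 = 0.0073 QALY.

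**4. Comparator.** The post-treatment and 3FU visits together carry 18 of the 23 weeks, so the assumed gain is 0.03 × 18/52 = 0.0104 QALY. The shift is 0.0022/0.0104 = 21% to 0.0073/0.0104 = 70% of it. At 12FU the same sustained difference is worth 0.03 × 57/52 = 0.033 QALY, and a one-SE shift is 14 to 57% of that.

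**5. Precision gained by adjustment.** The SE ratio is √(1 − r²), where r is the correlation of the area with baseline, r = [w₀ + ρ(1 − w₀)] / √(ρ + (1 − ρ)Σw²). At 3FU the weights are 0.217, 0.500 and 0.283, so Σw² = 0.377.

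| ρ | r at 3FU | SE ratio 3FU | SE ratio 12FU |
|---|---|---|---|
| 0.3 | 0.60 | 0.80 | 0.85 |
| 0.5 | 0.73 | 0.68 | 0.72 |
| 0.7 | 0.85 | 0.53 | 0.56 |

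For costs, assumed correlations of 0.2, 0.4 and 0.6 between baseline and follow-up cost give ratios of 0.98, 0.92 and 0.80.

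**6. Simulation check** (4,000 trials, 100 per arm, assumed SD 0.15, ρ 0.6, true difference 0.0104). Both estimators are centred on the truth (0.0103 each). The SD of the estimate is 0.0081 unadjusted and 0.0050 adjusted. Among trials with a baseline imbalance of more than 1.5 SE in favour of BIP TIC, the unadjusted estimate averages 0.0229 and the adjusted one 0.0103.

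**The case against.** The strongest reply is that the SAP is silent, not wrong. A reader might infer that it plans models with treatment as the only term. It does not say so: it excludes no covariate, and the methods paper it cites for the models is, by its title, about multiple regression of cost data. That stands, and the point is therefore that adjustment is not pre-specified. It does not remove the point, because a citation does not name a covariate.

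A second reply is that randomisation makes the unadjusted comparison unbiased. This also stands. A reader might call the problem bias, but the 1:1 allocation and the simulation averages do not support that. What remains is avoidable random error.

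A third reply is that the direction is unknown, since QALY gains might mean change from baseline. This is correct. On that reading the error changes sign, but it does not vanish, and stating the definition is part of the fix.

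Finally, this is a secondary objective and the sizes rest on assumed SDs and correlations. Both are true. The primary efficacy analysis is untouched.

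**Conclusion.** The point holds as an omission that is free to repair. No baseline adjustment is pre-specified for QALYs or costs, both baselines are collected, and using them would reduce the SE of the 3FU QALY difference to about 0.80 to 0.53 of its unadjusted value at assumed correlations of 0.3 to 0.7. The benefit for costs is smaller.

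Three stronger readings are not supported.
- **That the whole imbalance passes into the result.** This would need a correlation of 1 between visits. Under the assumed range, 45 to 77% is carried at 3FU.
- **That ordinary imbalance would reverse or double the result.** Shifting the estimate by the full 0.0104 QALY needs an imbalance of 2.4 SE at SD 0.12 and ρ 0.5 (two-sided chance about 1.7%), and 4.8 SE at SD 0.08 and ρ 0.3. Only at the extreme corner, SD 0.16 and ρ 0.7, does 1.4 SE suffice (about 15%). The conditional result in the simulation likewise comes from the upper part of the assumed range.
- **That every ICER is affected.** Of the six at each horizon, the three cost-per-QALY ratios are exposed through utility, with those in perspectives 2 and 3 also exposed through cost. Cost per responder in perspectives 2 and 3 is exposed through cost only. Cost per responder in perspective 1 contains neither baseline and is not exposed.

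**What to change.** In SAP 5.2, before unblinding, state that:
- QALYs are total area under the curve, and whether the child or the parent KIDSCREEN-10 supplies the utility;
- QALYs are regressed on treatment plus baseline mapped utility, at both horizons;
- costs in perspectives 2 and 3 are regressed on treatment plus baseline TiC-P cost, at both horizons (perspective 1 has no baseline cost);
- the adjusted arm differences are the ones used in the ICERs and the acceptability curve. If a model uses a non-identity link, the difference should be taken between adjusted mean predictions for the two arms. The SAP does not say how the uncertainty behind the curve is generated, so the same sentence should name the method and apply it to the adjusted models.

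The cost is a few sentences and one covariate per model, with no new data. If group allocation is already known to the analysts when the change is made, SAP 1.1 requires it to be labelled post-hoc.
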